### 2.4. Sample Size

As this is a pilot feasibility study, formal a priori power analysis was not conducted. The sample size of 38 students represents a convenience sample limited by the ecological environment of the classroom. Therefore, hypothesis testing in this protocol is not intended to provide confirmatory evidence of superiority, but rather to calculate the preliminary effect size and variance to inform the power calculation for future, fully powered multicenter trials.

### 2.5. Randomization and Masking

Given the nature of practical teaching (in which groups are pre-established by enrollment), simple individual randomization is not possible. Therefore, a cluster randomization design will be implemented. An independent researcher not involved in the teaching process will use (RANDOM.ORG; Randomness and Integrity Services Ltd., Dublin, Ireland) computerized random number generation software to assign the practice shifts (clusters) to either the CG or EG arm. Allocation concealment is ensured as the assignment will only be revealed to the Principal Investigator and students on the first day of the intervention.

Given the highly experiential nature of the intervention, participant blinding to the educational differences between conditions is likely only partial. However, participants will remain naive to the comparative study hypothesis and their specific allocation to either the control or experimental cohort. However, due to the logistical requirements of the intervention (the distribution of specific login codes), the Principal Investigator (PI) cannot be blinded during the sessions. To mitigate bias and ensure external control, statistical data analysis will not be performed by the PI. Instead, it will be performed by a different researcher (the co-author) who was not involved in the teaching process, using a dataset in which the group assignment is masked (coded as Group A vs. Group B).

To maintain this blinding and prevent the participants from distinguishing between the narrative formats (generic vs. adapted), the intervention relies on the physical and temporal separation of the clusters. Since Group A and Group B attend consecutive but distinct shifts, there is no simultaneous visual contact with the screens of the Control and Experimental groups. Furthermore, the clinical content and the structure of the Google Forms (Google LLC, Mountain View, CA, USA) remain visually identical for both groups; only the Wix interface ‘wrapping’ differs, and this is not visible to the other group due to the shift separation.

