### 2.6. Recruitment Strategies

Recruitment will be conducted using a saturation strategy of the available academic cohort. Potential participants will be approached during the introductory briefing of the first scheduled session. Due to the academic nature of the setting, the recruitment period is restricted to this initial contact point to ensure all students start the intervention simultaneously.

The PI will present the study objectives and the “Patient Information Sheet” to the entire class. To mitigate the potential for coercion given the teacher-researcher dual role, the recruitment protocol strictly differentiates between educational participation and research participation: all students will engage in the gamified sessions as part of their standard curricular training; only the data of those students who voluntarily sign the Informed Consent will be processed for analysis; no financial incentives will be offered. Participants in the CG are guaranteed access to the experimental platform after the study concludes (post-Session 4) to ensure equitable learning opportunities.

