The total cohort of 38 students will be divided into two consecutive practice shifts (Group A and Group B): one with 18 students and the other with 20. In the first session, software will be used to randomly assign which group will have the first shift. Students will remain in their assigned group for all four sessions to avoid cross-contamination. The program consists of four compulsory thematic modules:-Session 1: Prenatal care;-Session 2: Maternal-fetal assessment and well-being;-Session 3: Obstetric risk triage;-Session 4: Critical management in pregnancy.

Each day of the internship follows the same 120 min (2 h) time structure, which is visually summarized in Figure 2.

During the middle 60 min (intervention), the PI will monitor activity as the students interact with their devices. In the CG, all learners receive the same login URL and password, and the storytelling in Wix is standard. The mechanics are the same for everyone: progress bars are present, and points are awarded for correct answers. In the EG (PPDS-Adapted Gamification), at the beginning of each session, the PI provides differentiated codes (according to role) based on the learner’s profile to access five parallel narratives in Wix for the same clinical case. The clinical goal is the same for all participants, but the narrative “wrapping” and side mission change.

To ensure fidelity, the PI will be the only person with admin privileges in Wix and access to the Google Forms answers in real-time. Attendance will be monitored using signatures. The PI will resolve technical or clinical questions during the session, ensuring that the password lock in Wix does not impede the progress of learning.

Forms will be set up as “required steps” within the Wix narrative. In the case of the EG, the knowledge forms will be identical in content but esthetically matched to the identified player’s profile.

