A descriptive analysis of sociodemographic data and previous experience will be carried out, qualitative variables will be presented as absolute and relative frequencies, and quantitative variables will be presented as medians and interquartile ranges (if the distribution is not normal) or means and standard deviations if the distribution is normal.

To compare the overall efficacy (CG versus EG), the homogeneity at baseline will be checked. The Pre-test (Form 0) scores and the average grades according to academic records will be compared between both groups using the Mann–Whitney U test to ensure that the groups are comparable despite the cluster randomization. Additionally, prior gamification exposure and the distribution of PPDS profiles will be descriptively compared at baseline to identify any major initial imbalances between the clusters

To test the primary hypothesis, the mean global LG of the four sessions between the CG and the EG will be compared using the Mann–Whitney U test for independent samples. Given that the study design involves two natural clusters of unequal size (n = 18 and n = 20), the main hypothesis test will be performed at the participant level. Given the limitation of having only one cluster per arm, inferential statistics will be considered strictly exploratory, and results must be interpreted with caution.

Regarding the secondary outcomes, the analysis of the five PPDS profiles will be strictly descriptive and exploratory, given the limited sample size. Subdividing the experimental group (n = 20) into five profile categories yields cell sizes too small for robust inferential statistics; hence this approach prioritizes statistical rigor by avoiding underpowered hypothesis testing on these specific sub-variables.

To analyze the students’ perception at the end of the study, the satisfaction scores (GAMEX) will be compared between groups using the Mann–Whitney U test. Finally, an exploratory Spearman correlation analysis will be performed between satisfaction and LG to determine if the students who enjoyed the experience the most were also those who learned the most.

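### Concealment and masking are asserted but not secured, allocation is described inconsistently, and shift order is drawn once with no alternation described

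*Protocol article*

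**What the plan says.** **Timing.** In Section 2.5 an independent researcher randomises the two practice shifts to an arm, and "the assignment will only be revealed to the Principal Investigator and students on the first day of the intervention". Section 2.6 states that "Potential participants will be approached during the introductory briefing of the first scheduled session". The PI makes that presentation. Every student takes the sessions, but only those who consent are analysed.

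**Masking.** The next paragraph of Section 2.5 concedes that participant blinding is probably partial, then says that "participants will remain naive to the comparative study hypothesis and their specific allocation". The analyst is a co-author outside the teaching, who works on data coded Group A and Group B. The same section uses those names for the shifts themselves: "Since Group A and Group B attend consecutive but distinct shifts".

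**Allocation.** The Abstract has students assigned by natural practice group. Section 2.5 randomises shift to arm. Section 2.7 says that in the first session "software will be used to randomly assign which group will have the first shift". It gives the group sizes as 18 and 20 without tying either to an arm. Section 2.10 nevertheless writes "Subdividing the experimental group (n = 20) into five profile categories".

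**Order.** Section 2.7 keeps students in their group for all four sessions. No second draw of order and no alternation is described.

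**The concern.** Concealment in a cluster trial depends on consent and baseline being complete before anyone who can influence them knows the arm. Here disclosure, a software draw and consent share one day, and the person seeking consent is also the teacher who learns the arm. Knowledge of the arm could affect who agrees to data use and how students answer the pre-test and the Player Personality and Dynamics Scale (PPDS).

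The conflicting accounts mean a reader cannot tell what was randomised or whether the result was already known. The analyst mask is one of the stated protections against the PI's dual role (Section 4), so a mask that can be read through weakens that protection.

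With consecutive shifts and one cluster per arm, anything that differs between going first and going second cannot be separated from the intervention. Examples are paper test items passed on between shifts, time of day, and the PI running the case a second time. Sections 2.4 and 2.10 make effect-size estimation the pilot's main statistical purpose, so a distortion of that estimate passes into the planning of the next trial.

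**Working it through.** **1. Sequence on day one.** Disclosure is on the first day of the intervention (2.5). Consent is sought at the briefing of the first session (2.6). The Section 2.7 draw is also in the first session. Form 0 is the first paper form (2.9), but the text gives no hour for it. No sentence orders these four events. Figure 1, the assessment schedule, is not available here and may do so.

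**2. Allocation.** The sizes reproduce: 18 + 20 = 38. Two clusters and one per arm give C(2,1) = 2 possible allocations, so either shift has probability 1/2 of being experimental. Stating the experimental group as 20 leaves one allocation. That is either a slip or an allocation already made. Sections 2.5 and 2.7 may describe one draw or two (arm, then order); the text does not say which.

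**3. Masking.** The masked codes equal the shift names. If nearly all students consent, the dataset holds about 18 and 20 records, and the published experimental size of 20 points to the arm.

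**4. Share of an order effect in the arm contrast.** Let k be the number of the four sessions in which the experimental group goes second. For a constant order effect, the share carried into the averaged learning-gain contrast is (k − (4 − k))/4.
- k = 4: (4 − 0)/4 = 100%
- k = 3: (3 − 1)/4 = 50%
- k = 2: (2 − 2)/4 = 0%

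At k = 0 the share is 100% with the sign reversed.

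**5. Illustration of size.** The documents give no order effect and no SD, so the effect sizes here are assumptions in units of the SD of global learning gain. The naive standard error of the contrast is √(1/18 + 1/20) = 0.325 SD. The Mann–Whitney test was simulated with 18 against 20 independent normal observations, no true intervention effect, two-sided 0.05, and 8,000 runs per row. A normal approximation for two means is the cross-check.

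| Assumed order effect (SD) | Simulated rejection | Approximation |
|---|---|---|
| 0 | 4.9% | 5% |
| 0.2 | 9.3% | 8.9% |
| 0.3 | 13.8% | 15.0% |
| 0.5 | 30.6% | 33.7% |
| 0.8 | 63.9% | 69.2% |

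No figure is attached to the consent route, because the documents give no expected consent rate or reason for refusal.

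**The case against.** **Concealment.** A reader might infer that concealment fails. The documents do not show this. Disclosure could follow consent and baseline on the same day. Section 2.6 says that "The PI will present the study objectives and the “Patient Information Sheet” to the entire class" and that "the recruitment period is restricted to this initial contact point to ensure all students start the intervention simultaneously", which reads most naturally as one joint briefing before the shifts divide. On that reading no later shift consents after seeing the earlier one. Cluster membership is set by enrolment, so knowledge of the arm can act only through consent to data use and baseline answers. All of this stands. It leaves the order of consent, Form 0 and disclosure unstated in the text.

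**Order.** A reader might also infer that the order is fixed for all four sessions. Section 2.7 fixes the group, not the order, so the full confounding is conditional. Since Section 2.10 presents the article as the full protocol, with no separate analysis plan, the silence on alternation still deserves an answer.

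**Contamination.** It would be wrong to say the plan relies only on keeping screens out of sight. It changes passwords by session and group, requires confidentiality and keeps a field diary (4.1). It also makes detected contamination a withdrawal criterion (2.3) and a feasibility outcome (2.8). Passwords do not protect paper tests, and none of these measures addresses time of day or the PI's practice.

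**Already conceded.** Section 4.1 admits confounding with cluster-level differences and calls the comparison exploratory. This is right, but shift order is not named, and unlike the other cluster differences it can be balanced by design.

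**Cancellation.** Learning gain is post-test minus pre-test, so an order effect equal on both scores would cancel. If the pre-test is taken once on Form 0, as the baseline comparison in Section 2.10 suggests, items passed on during later sessions would act on the post-tests alone.

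**Conclusion.** The point holds as a failure to secure concealment and masking, not as proof that either has broken down. Three parts need no assumption: students cannot both be told their allocation and remain naive to it; the accounts in the Abstract and Sections 2.5, 2.7 and 2.10 do not agree on how allocation happens or whether it is settled; and the analyst's codes are the shift names.

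The order-effect part rests on the first-session order being kept. If it is, 100% of a constant order effect enters the arm contrast; with two sessions each way, none does. The size of any such effect is unknown. The 14% rejection rate at 0.3 SD is an illustration that also assumes independent students and no other cluster difference. Calling the analysis exploratory limits what will be claimed from the p-value, but it does not protect the effect estimate the pilot exists to supply.

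**What to change.** - State that whole-class consent and Form 0 (pre-test, PPDS, demographics) are completed before the independent researcher discloses the arm. This needs one short meeting, or an explicit sequence within the existing briefing.
- Reconcile the Abstract and Sections 2.5, 2.7 and 2.10 to one allocation procedure, saying whether arm and order are one draw or two. Write the experimental group's size as 18 or 20 depending on the draw.
- Remove either the statement that students are told the assignment or the claim that they are naive to it.
- Give the analyst neutral codes unrelated to the shift names.
- Alternate which group goes first, two sessions each. If the timetable prevents this, name shift order as a confounder in Section 4.1.

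Most of this is wording. The real cost is a timetable swap in two sessions, which needs agreement. Alternation balances a constant order effect only; the confounding from one cluster per arm remains.

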### 2.6. Recruitment Strategies

Recruitment will be conducted using a saturation strategy of the available academic cohort. Potential participants will be approached during the introductory briefing of the first scheduled session. Due to the academic nature of the setting, the recruitment period is restricted to this initial contact point to ensure all students start the intervention simultaneously.

The PI will present the study objectives and the “Patient Information Sheet” to the entire class. To mitigate the potential for coercion given the teacher-researcher dual role, the recruitment protocol strictly differentiates between educational participation and research participation: all students will engage in the gamified sessions as part of their standard curricular training; only the data of those students who voluntarily sign the Informed Consent will be processed for analysis; no financial incentives will be offered. Participants in the CG are guaranteed access to the experimental platform after the study concludes (post-Session 4) to ensure equitable learning opportunities.

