## Abstract

**Background/Objectives**: Simulation-based education often lacks personalization, focusing on technical competence rather than individual student profiles. This protocol describes a study designed to evaluate whether adapting gamified narratives to nursing students’ personality profiles has the potential to support academic performance in obstetrics. This study aims to validate the integration of psychometric profiling and AI as a sustainable strategy for personalized clinical training. **Methods**: A cluster-randomized controlled longitudinal pilot trial will be conducted at the University of Atlántico Medio. The protocol has been submitted for registration at ClinicalTrials.gov (Registration Pending). Thirty-eight second-year nursing students meeting inclusion criteria (excluding repeaters or those with prior specialized training) will be assigned by natural practice to either a control group (generic gamification) or an experimental group (gamification adapted according to Player Personality and Dynamics Scale profiles using AI-generated content). The intervention comprises four clinical simulation sessions focusing on pregnancy and childbirth, which are managed via the Wix platform. The primary outcome is academic performance, measured as “Learning Gain” (post-test scores minus pre-test scores). Secondary outcomes include student satisfaction measured via the Gameful Experience Scale. Data will be analyzed using Mann–Whitney U tests to compare overall efficacy and intragroup evolution. To minimize observer bias, knowledge assessments will utilize automated, objective scoring, and participants will be blinded to the study hypothesis. **Expected Outcomes**: The study aims to establish the technical and pedagogical feasibility of integrating AI-adapted narratives into nursing curricula. It is anticipated that the personalized approach will show positive trends in learning gains and engagement patterns, providing a baseline for larger multicenter trials. **Conclusions**: This protocol presents a framework for “Precision Education” in nursing, shifting from “one-size-fits-all” simulations to student-centered adaptive training. The use of Generative AI makes such personalization sustainable and cost-effective for health science faculties.

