Consequently, the aim of this study is to evaluate the effectiveness of a profile-adapted gamified intervention compared to a generic gamified intervention in improving the academic performance of nursing students regarding obstetric competencies upon completion of the four-week program. Based on this aim, the following hypotheses are proposed:-Primary hypothesis—the Experimental Group (EG), with exposure to the profile-adapted narrative, will demonstrate a significantly higher global Learning Gain (LG) compared to the Control Group (CG) receiving generic gamification.-Secondary hypothesis—there is a positive correlation between the level of student satisfaction and academic performance (LG) regardless of the group.

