Given the educational nature of the intervention, the risk of physical harm is negligible. However, specific protocols have been established to mitigate potential psychological, technical, and ethical risks. To ensure clinical and ethical safety, all narratives and clinical cases generated with the assistance of Generative Artificial Intelligence will be reviewed, corrected, and validated by the PI. This process guarantees that the content is free from gender bias, racial stereotypes, or erroneous clinical recommendations (hallucinations). To prevent potential offense or stigmatization arising from the PPDS profiles, students will be explicitly informed during the briefing that these categories are strictly playful archetypes for game mechanics and do not constitute a psychological or clinical diagnosis. In the event of persistent technical failures, the session will immediately revert to a traditional seminar format to prevent student anxiety or loss of learning time. The PI will maintain a “Field Diary” to record any spontaneous reports of student distress, technical incidents, or expressions of dissatisfaction. Any event requiring the interruption of a student’s participation will be reported to the Ethics Committee.

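### Students are said to be blinded to the hypothesis and to their own allocation, but the protocol's own allocation and recruitment steps do not deliver this, and the self-reported GAMEX comparison is the outcome most exposed

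*Protocol article*

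**What the plan says.** The abstract lists, among the measures against observer bias, that "participants will be blinded to the study hypothesis", with no qualification. Section 2.5 goes further: "participants will remain naive to the comparative study hypothesis and their specific allocation to either the control or experimental cohort". Just before that sentence it concedes that "participant blinding to the educational differences between conditions is likely only partial", and the preceding paragraph, on allocation concealment, states that "the assignment will only be revealed to the Principal Investigator and students on the first day of the intervention".

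Section 2.5 rests the masking on the two shifts being apart in space and time, so that neither arm sees the other's screens.

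Section 2.6 describes the recruitment briefing. "The PI will present the study objectives" and the information sheet to the entire class. The Introduction gives the aim as to "evaluate the effectiveness of a profile-adapted gamified intervention compared to a generic gamified intervention". Section 2.6 also says: "Participants in the CG are guaranteed access to the experimental platform after the study concludes". No matching offer is made to the experimental group (EG). Section 2.11 adds that "students will be explicitly informed during the briefing that these categories are strictly playful archetypes for game mechanics".

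Section 4.1 foresees that control group (CG) students may find out about the EG missions and lose motivation, and that students may answer surveys so as to please the teacher.

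**The concern.** A report that follows this protocol would claim that students knew neither the hypothesis nor their arm. Readers would then take the satisfaction comparison as protected from expectation effects. Other sentences in the same document describe steps that tell students, or are likely to tell them, that two versions are being compared and which one they have.

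GAMEX is the outcome where this matters most. It is self-reported, collected once at Session 4, and compared between arms with a Mann–Whitney U test (Section 2.10). A student who believes the tailored version is the one under test may rate it higher, and a student who learns of going without it may rate the generic version lower. Section 5 names learning gains or satisfaction as the basis for judging whether larger trials are warranted, so a distorted GAMEX difference would feed a real decision even in a pilot.

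**Working it through.** The plan states no figure on this point, so the check sets the passages side by side: each route by which a student could learn the comparison or the arm, how firm the evidence is, and whether shift separation closes it.

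1. **Reveal on the first day (Section 2.5).** The sentence before it concerns assigning shifts to the CG or EG arm, so what is revealed reads as the arm. A student who is told the assignment cannot be unaware of it. This contradicts the naivety claim directly, within one section. Shift separation is irrelevant to it.
2. **Objectives presented to the whole class (Section 2.6).** If they are presented as the Introduction states them, the comparison of adapted with generic gamification is disclosed. The information sheet is not shown, so the exact wording is unknown. Shift separation does not close this route, because the briefing is addressed to everyone.
3. **Later access for controls only (Section 2.6).** Once told, this informs controls that another version exists and that they do not have it. The time of telling is not stated; that it comes before GAMEX is inferred from its place in the recruitment section. Shift separation does not close it.
4. **Talk between classmates (Section 4.1).** The protocol itself expects it. Passwords that change by session and group, and a confidentiality agreement, reduce it; the field diary only records it. Shift separation does not stop conversation outside class.
5. **Profile explanation and parallel narratives (Sections 2.11 and 2.7).** These show EG students that content is tailored. They do not by themselves reveal that another arm exists, so they count only as support.

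Route 1 is a contradiction on the page. Routes 2 and 3 are likely but depend on wording and timing that are not shown. Route 4 is acknowledged and partly mitigated.

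**Which outcomes are exposed.** GAMEX is exposed directly, as self-report. Learning gain comes from multiple-choice tests with objective correction, so knowing the arm can act on it only through effort or demoralization.

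**Size.** No expectation effect is given or derivable. As an illustration only, suppose GAMEX shifts by 0.2 to 0.5 SD (assumed, not from the documents) and the 18 and 20 students are treated as independent:

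- SE of the standardised difference = √(1/18 + 1/20) = √(0.0556 + 0.0500) = 0.325.
- 0.2 / 0.325 = 0.6 SE; 0.5 / 0.325 = 1.5 SE.
- In 10,000 simulated Mann–Whitney tests (two-sided 0.05 assumed, normal data, no true effect), p < 0.05 occurred in about 9% at 0.2 SD and 30% at 0.5 SD, against about 5% with no shift.

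This ignores clustering. With one cluster per arm, the true standard error is larger than 0.325 wherever shifts differ, so the ratios of 0.6 and 1.5 are upper bounds for the assumed shifts. They show what such a shift would do, not that one will occur.

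**The case against.** The best defence is that the protocol is already candid. Section 2.5 admits incomplete blinding to the educational differences. Section 4.1 names demoralization and the wish to please the teacher and lists countermeasures, including anonymous satisfaction surveys. Efficacy inference is labelled exploratory in Sections 2.10 and 4.1, and GAMEX is secondary. The first-day reveal could also be meant loosely, as students learning their shift and login rather than an arm label.

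Much of this stands, and it limits the weight of the point. It does not remove it. The concession covers the educational differences only; the next sentence reasserts naivety to hypothesis and allocation, and the abstract carries no qualifier. If the reveal concerns only the shift, the text should say so. Anonymity addresses pleasing the teacher, not expectation, and it sits awkwardly with the planned correlation of each student's GAMEX score with learning gain.

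Stronger readings are tempting and should be resisted:

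- A reader might infer that the trial is in effect open-label. The documents do not establish what students will actually know: the briefing wording and the timing of the promise to controls are not shown.
- A reader might infer that five narratives in one room disclose the hypothesis. They show tailoring, not the comparison.
- A reader might infer that bias would favour a stated GAMEX hypothesis. The Introduction states none between arms: the primary hypothesis concerns learning gain, and the secondary one is a correlation regardless of group.

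**Conclusion.** The point holds in limited form. The protocol claims that students are unaware of the hypothesis and of their arm, and its own steps do not deliver that. The firmest evidence is the clash within Section 2.5 between the first-day reveal and the claim of unawareness. The briefing on objectives and the access promised to controls alone add to it, on the assumption that students hear both before completing GAMEX.

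The effect is mainly on how the GAMEX comparison may be read. Learning gain is affected only indirectly. The magnitude is unknown. This is worth correcting before the study starts, but it does not undermine the pilot's exploratory purpose.

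**What to change.** 1. In Section 2.5, reconcile the first-day reveal with the statement on naivety. There and in the abstract, replace the blinding claim with wording to this effect: students are at most partly blinded, and the GAMEX comparison is to be read as unblinded self-report.
2. In Section 2.6, word the briefing neutrally: two versions of a gamified activity are being compared. Offer both shifts access to the other version after Session 4, and use neutral labels and codes for versions and profiles. Students still learn that a comparison is made, so consent remains honest.
3. Optionally, add one Session 4 item, placed after GAMEX, asking students to guess their arm or the study hypothesis, and report it by arm. Asking instead whether the story seemed adapted would check delivery of the intervention, not blinding.

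Any change to when the profiles are explained would have to be reconciled with Section 4.1, which uses that explanation to reduce socially desirable answers.

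The cost is edits to the text, briefing and information sheet, a weaker blinding statement in the abstract and, if the option is taken, one extra item in a study that is already wary of survey fatigue.
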